### 2.8. Interventions

A sum of 60 patients from the China medical university will be divided into 2 groups. In both the INT group and CON group, A qualified acupuncture doctor with at least 2 years of clinical experience will provide the intervention sessions on both groups. The acupuncture frequency will be 2 times a week for 6 weeks in both groups. Both groups will also receive routine Western medicine treatments.

### 2.9. Intervention group (INT)

In the intervention group, the patients will receive traditional Chinese medicine style acupuncture at the following points: ST36 (Zusanli), ST37 (Shangjuxu), ST39 (Xiajuxu), PC6 (Neiguan), and LI4 (Hegu) Liv 3 (Taichung) (Fig. 2). The points will be applied bilaterally. The effectiveness of those points in treating digestion (with the exception of Liv 3 [Taichung]) was shown in our previous research.^[27]^ The treatment will take place 2 times a week for 6 weeks. Totally 12 needles will be used in each intervention. Acupuncture sterile needles manufactured by “Yu Kuang” 40mm with 30G will be used for this study (Fig. 2).

**Figure 2. F2:**
[figure not shown]
Acupoints used in the intervention group. Intervention group acupoints: ST36 (Zusanli), ST37 (Shangjuxu), ST39 (Xiajuxu), PC6 (Neiguan), and LI4 (Hegu) liv 3 (Taichung).

As part of the acupuncture procedure, the acupuncturist will disinfect the acupuncture points with 70% alcohol and will insert the needles perpendicularly into the muscle layer at an approximate depth of 10 to 30 mm. The doctor will manipulate the needles upward and downward and will rotate the needles 180° in both directions in a search for the “De Chi” phenomenon. During the intervention, the patient will be positioned in a supine position. After 30 minutes the doctor will withdraw the needles.

### 2.10. Control group (CON)

The patients in the control group will receive bilateral shallow acupuncture (12 needles) on the sham points that are located 1 cm lateral/medial and 1 cm distal/proximal to the following acupoints: ST36 (Zusanli), ST37 (Shangjuxu), ST39 (Xiajuxu), PC6 (Neiguan), and LI4 (Hegu) liv 3 (Taichung) (Fig. 3). Those points are in a location of 1 cm lateral/medial and 1 cm distal/proximal to those points and are not known as acupuncture points. The needle insertion will be a perpendicular shallow insertion into the skin tissue level. The acupuncture doctor will use the needle with tube insertion for needle insertion and will leave the needle in the depth of the tube insertion (approximately 4 mm depth into the skin) without needle manipulation. The needles will be retained for 30 minutes. In addition to the sham points, the patients in this group will also receive routine Western medicine treatment as per each patient’s needs. The treatment frequency and skin disinfection will be identical to the treatment group.

**Figure 3. F3:**
[figure not shown]
Sham acupoints used in the control group. The red dots represent the sham points used in the control group.

### 2.11. Drug treatment

All patients will receive drug treatments as prescribed by their doctor. This study will not alter any drug intervention.

### 2.12. Outcome measures

Main outcome measurements are: body weight, BMI (will be measured weekly) dumping syndrome questioners: the Sigstad’s score in order to determine the diagnosis of dumping syndrome and the Arts’ dumping questionnaire in order to assess early or late dumping syndrome (will be measured on the baseline, week 3, week 6) (see Figure S1, Supplemental Digital Content, http://links.lww.com/MD/J34 for the Sigstad’s score and Figure S2, Supplemental Digital Content, http://links.lww.com/MD/J35 for the Arts’ dumping questionnaire).

The secondary outcomes are: muscle grip strength test (measured weekly in kg) (by electronic hand grip test model EH101 manufactured by “CAMRY,” China), blood test: Complete Blood Count, kidney and electrolytes (measured as adjuvant adjuvant concurrent chemoradiation therapy schedule), pre-albumin, albumin level, glucose blood levels, inflammation data including Erythrocyte Sedimentation Rate and C-reactive protein (measured at baseline and on week 6). Total Intensive care unit stay, total hospital stay, and total mechanical ventilation in days will be measured 6 months after inclusion. Mortality will be measured at 3 months, 6 months. Medical charts and drug use will also be measured (Fig. 4). All measurements will be measured by nurses and doctors in the department that are blind to the study group allocation.

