## Abstract

**Methods::**

Sixty advanced esophageal cancer patients post-feeding jejunostomy will be divided into 2 equal groups, an intervention group (n = 30) and a control group (n = 30). Patients in the intervention group will receive acupuncture using the following acupoints: ST36 (Zusanli), ST37 (Shangjuxu), ST39 (Xiajuxu), PC6 (Neiguan), LI4 (Hegu), and Liv 3 (Taichung). Patients in the control group will receive shallow acupuncture on 12 non-acupoints (sham points), 1 cm from the above mention points. Patients and assessors will be blind to trial allocation. Both groups will receive acupuncture twice a week for 6 weeks. The main outcome measurements are: body weight, BMI, Sigstad’s score, and the Arts’ dumping questionnaire.

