### 2.14. Sample size calculation

Since no previous similar study was conducted, the sample size was determined via the G*Power version 3.1.9.4 software calculation, based on a large effect for a two-tailed *t* test. The calculation showed that a total of 26 patients were needed. However, to account for a 15% patient drop-out expected frequency. For 80% power with an effect size of 0.8, a total of 60 patients were required, with 30 patients in each group.

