### 2.16. Statistical analysis

The statistical analysis for all measurements will analyze changes from baseline and changes over time. Categorical data will be presented as a percentage (n %), while continuous data will be presented as mean ± standard deviation. For changes from baseline the paired *t* test will be used. The independent *t* test or the Mann–Whitney *U* test will analyze continuous variables depending on applicability, and the Chi-square test or Fisher’s exact test (as appropriate) will be used for categorical variables. For repeat measurements data the repeat measures ANOVA will be used. The IBM SPSS Statistics version 22.0 (SPSS Inc, Chicago, IL) will be used for data analysis, and significance will be determined at a *P* value < .05. If applicable, a subgroup analysis will be done on tumor stage, age, BMI, dumping syndrome status at baseline and dumping syndrome type. If there are any missing data, they will be imputed using multiple imputations (if applicable).

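### Four main outcomes are left unranked, each at P < .05 with an open switch between them, so no single claim carries the stated error rate or power

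*Protocol article*

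**What the plan says.** - **Outcomes.** The Abstract (Methods) states: "The main outcome measurements are: body weight, BMI, Sigstad’s score, and the Arts’ dumping questionnaire". Section 2.12 repeats the same four ("Main outcome measurements are: body weight, BMI (will be measured weekly) dumping syndrome questioners"). Weight and BMI are weekly; the two questionnaires are taken at baseline, week 3 and week 6. A separate list is labelled secondary, so the four form the top tier.
- **Testing.** Section 2.16: "The statistical analysis for all measurements will analyze changes from baseline and changes over time". The threshold is "significance will be determined at a *P* value < .05". The section lists paired t, independent t or Mann–Whitney tests, and repeated-measures ANOVA for repeated data. It states no order of testing and no adjustment.
- **Sample size.** Section 2.14 is "based on a large effect for a two-tailed *t* test" and concludes: "For 80% power with an effect size of 0.8, a total of 60 patients were required, with 30 patients in each group". It ties the effect size to no outcome.
- **Aims.** The hypothesis that closes Section 1 concerns dumping syndrome. Section 2.1 puts dumping first and adds malnutrition through weight and BMI. The Abstract (Discussion) says the results will answer both questions.
- **Switch.** The limitations paragraph of Section 3 says that, if the number developing dumping is low, weight and BMI become the focus as main outcomes. It does not say how low, who decides, or whether the decision is made blind to allocation.

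**The concern.** A confirmatory trial needs to say in advance which result makes it positive. Here four outcomes stand level, each against 5%, and the emphasis may move between them once the frequency of dumping is known. A reader of the final report could not tell whether a significant weight result alone, or a significant questionnaire score alone, is the success the trial was designed to show.

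Three things are at stake. The chance of at least one false positive among the main outcomes exceeds 5%. The 80% power describes a single comparison that the protocol never identifies. And weight and BMI could be reported as two findings when they are close to one.

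**Working it through.** **1. The plan's own figure.** Inputs from Section 2.14: two-sided t test, d = 0.8, 80% power, 15% drop-out. That section gives no alpha; 0.05 is taken from Section 2.16. The two-sample t test (noncentral t) needs 25.5, so 26 per group. Inflating, 26 × 1.15 = 29.9, so 30 per group and 60 in total, as stated. (Dividing instead, 26 / 0.85 = 30.6, gives 31 per group.) The figure therefore reproduces for one test at 0.05. It does so only with 26 read as a per-group number, although the text says "The calculation showed that a total of 26 patients were needed"; that is a separate matter.

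**2. Error rate if any one main outcome suffices, tests independent.** Rate = 1 − 0.95^k.

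| Tests k | Rate | Multiple of 5% |
|---|---|---|
| 2 | 9.75% | 1.95 |
| 3 (weight and BMI as one) | 14.3% | 2.85 |
| 4 | 18.5% | 3.7 |

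**3. Allowing for correlation.** The document gives no correlations, so these are assumptions: weight with BMI 0.90 to 0.999; Sigstad with Arts 0 to 0.9; weight or BMI with either questionnaire 0 to 0.5. Four two-sided 5% tests were simulated as multivariate normal (2 million draws per setting), one test per outcome:

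| Weight–BMI | Sigstad–Arts | Cross | Rate | Multiple |
|---|---|---|---|---|
| 0.90 | 0 | 0 | 16.1% | 3.2 |
| 0.98 | 0 | 0 | 15.1% | 3.0 |
| 0.98 | 0.5 | 0.2 | 14.3% | 2.9 |
| 0.98 | 0.7 | 0.3 | 13.4% | 2.7 |
| 0.98 | 0.9 | 0.5 | 11.6% | 2.3 |
| 0.999 | 0.9 | 0.5 | 11.0% | 2.2 |

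The full range is 11.0% to 16.1%.

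**4. Weight and BMI.** BMI = weight / height². With adult height fixed over six weeks, the percentage changes are identical. For absolute changes, assume height 1.66 m (SD 0.07), weight-change SD 3 kg and mean loss 1 to 4 kg: the correlation is 0.990 to 0.996. This redundancy lowers the family-wise rate: with the other tests independent, merging the two moves it from 18.5% to 14.3%.

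**5. Power under different allocations of alpha.** Evaluable patients: 60 × 0.85 = 51, split 25 and 26; d = 0.8 assumed for every outcome tested.

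| Two-sided alpha | Use | Power |
|---|---|---|
| 0.05 | one primary | 79.9% |
| 0.025 | first Holm step, two primaries | 70.6% |
| 0.0125 | Bonferroni over four | 60.5% |

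**The case against.** The article condenses a fuller plan, and an unseen SAP may hold a multiplicity rule and an analysis time point. That is fair, and the absence of either is not the finding. What stands is what the article itself fixes: four outcomes on one level, one flat threshold, a sample size tied to none of them, and an untriggered switch. Choosing the primary outcome is a protocol decision, because the sample size rests on it.

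Nor does the document state that any single positive outcome means success. This is also fair; the inflation figure is conditional on that rule. But no other rule is given, and the power statement lacks an outcome under any rule.

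A partial order can be read into the text, with dumping first and weight second. It does not settle the matter: dumping has two instruments, Section 2.12 ranks neither above weight, and the switch can reverse the order.

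Three stronger readings are tempting but not supported:

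- *The error rate is simply three times nominal.* Three times lies in the upper part of a range that depends on assumed correlations. Both questionnaires measure dumping, so a high correlation between them, and a rate nearer 11%, is plausible.
- *Success can be declared at any visit, so the rate is higher still.* Section 2.16 assigns repeated data to repeated-measures ANOVA, which points to one longitudinal test per outcome. The t tests also listed leave some ambiguity, but separate claims at each visit are not established.
- *Counting BMI beside weight is what drives the inflation.* The redundancy reduces it. The fault is counting one piece of evidence twice.

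**Conclusion.** The point holds and should be corrected before the results are seen. As written, no outcome is fixed in advance as the one that decides the trial, and the switch in Section 3 confirms this. If any one main outcome may carry the claim, the family-wise false-positive rate is about 11% to 16%, roughly 2 to 3 times 5%. That rests on the any-one-suffices rule, one test per outcome and the assumed correlations. No figure is put on the switch, because the document does not say how it would be triggered. The conclusions that the 80% power attaches to no defined claim, and that BMI adds almost nothing independent of weight, do not depend on the assumed correlations among the four test results.

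**What to change.** Before unblinding, in the protocol and the registry entry:

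1. Name either one primary outcome, or one for each stated aim: one dumping score and per cent change in body weight, both at week 6. Test two primaries with Holm's method at overall two-sided 0.05.
2. Make BMI, the remaining main outcomes and all other visits secondary, reported as estimates with 95% confidence intervals.
3. Reword Section 2.14 so that the effect size, alpha and power refer to the named primary.
4. Delete the switch in the limitations paragraph of Section 3, or replace it with a rule fixed in advance, with a numerical trigger, applied blind to allocation.

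No new data or visits are needed. One primary costs no power. With two, the first Holm step costs up to about 9 points per outcome (79.9% to 70.6% at d = 0.8 with 51 evaluable). Holding 80% at that step would take 31 evaluable per group, or 31 / 0.85 = 36.5, so 37 enrolled per group and 74 in total. Keeping all four under Bonferroni would cost about 19 points (79.9% to 60.5%), so narrowing the set now is the cheaper course.

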Limitations of the study include a specific Taiwanese population and cannot be generalized to other populations. This study is also only a single-center study. The study protocol could not apply a double-blind design due to the type of intervention (manual acupuncture). The study will investigate the role of acupuncture in the prevention of dumping syndrome and malnourishment, the study does not require a positive Sigstad’s score to verify dumping syndrome as a condition for inclusion, therefore it is possible that the number of patients that will develop dumping syndrome could be low, in this case, the study will focus on body weight and BMI as the main outcomes to assess the prevention of malnourishment. The study did not specify the cancer stage in the inclusion criteria. High mortality rates in Esophagus cancer might impair the completeness of the data and can increase the levels of missing data.

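### Six-month totals of hospital, ICU and ventilation days take no account of death, so they can mislead in either direction if mortality or its timing differs between arms

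*Protocol article*

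**What the plan says.** Section 2.12 (Outcome measures) of the protocol article places three resource-use measures among the secondary outcomes: "Total Intensive care unit stay, total hospital stay, and total mechanical ventilation in days will be measured 6 months after inclusion". The next sentence makes death an outcome of its own: "Mortality will be measured at 3 months, 6 months". The section does not connect the two.

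Section 2.16 (Statistical analysis) covers every outcome: "The statistical analysis for all measurements will analyze changes from baseline and changes over time". A 6-month total has no baseline value and is recorded once, so the paired t test and the repeated-measures ANOVA do not apply to it. What remains is the comparison in which the independent t test or the Mann–Whitney U "test will analyze continuous variables depending on applicability". The missing-data rule is general: "If there are any missing data, they will be imputed using multiple imputations (if applicable)".

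The limitations paragraph in section 3 (Discussion) warns: "High mortality rates in Esophagus cancer might impair the completeness of the data and can increase the levels of missing data". Death is presented there only as a cause of missing data.

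**The concern.** Hospital, ICU and ventilator days can accrue only while a patient is alive. A patient who dies at the end of week 2 can contribute at most 14 hospital days; a survivor can contribute up to about 180. A raw total therefore cannot separate a patient who needed little hospital care from one who did not live long enough to need it.

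Both readings of the stated plan run into trouble. If patients who die keep the total they had reached, an early death is scored as a short stay. If death is treated as missing data, as the limitations paragraph suggests, the multiple-imputation rule would generate hospital days for people who have died.

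At stake is the interpretation of three secondary outcomes in a population where deaths within 6 months are expected. A difference in days could be read as benefit or harm when it partly reflects who survived.

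**Working it through.** The plan states no figure for these outcomes that could be reproduced, so the check is whether the mechanism has a material size.

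**Inputs from the documents:** 6-month window (section 2.12); 30 patients per arm (section 2.14); significance at P < .05 and the two candidate tests (section 2.16); mortality described as high, with no rate (section 3).

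**Assumed inputs, not in the documents:** 6-month mortality of 20%, 30% or 40% in one arm; a doubled death hazard in the other; exponential survival; the same share r of days alive spent in hospital in both arms, with r = 25%; no extra inpatient days before death.

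**Step 1: mean days alive.** With T = 180 days and 6-month mortality m, mean days alive are A = T × m / (−ln(1 − m)). Doubling the hazard changes mortality to 1 − (1 − m)². For m = 0.30 this is 1 − 0.49 = 0.51. Then A = 180 × 0.30 / 0.3567 = 151.4 days, against 180 × 0.51 / 0.7133 = 128.7 days.

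**Step 2: hospital days, and days alive and out of hospital.** Hospital days are r × A; days alive and out of hospital are (1 − r) × A.

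| 6-month mortality | Mean days alive | Hospital days (25%) | Difference | Days alive and out of hospital |
|---|---|---|---|---|
| 20% v 36% | 161.3 v 145.2 | 40.3 v 36.3 | 4.0 | 121.0 v 108.9 |
| 30% v 51% | 151.4 v 128.7 | 37.9 v 32.2 | 5.7 | 113.5 v 96.5 |
| 40% v 64% | 141.0 v 112.8 | 35.2 v 28.2 | 7.0 | 105.7 v 84.6 |

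The arm with more deaths has 4 to 7 fewer hospital days although hospital use per day alive is identical. Days alive and out of hospital rank the arms the other way.

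**Step 3: what this does to a test with 30 per arm.** Letting the hospital share vary between patients as Beta(2,6) (mean 25%), the standard error of the difference is about 7 days. The higher-mortality arm is significantly favoured in about 8%, 14% and 18% of simulated trials in the three rows, against a nominal 2.5%.

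**Step 4: inpatient days before death.** If each death brings k extra inpatient days, the truncation effect is cancelled when k = r × (A₀ − A₁) / (m₁ − m₀). In the middle row at r = 25%, k = 5.68 / 0.21 = 27 days. At r = 1%, a plausible level for ICU or ventilation, the truncation effect is only 0.01 × 22.7 = 0.23 days and k = 0.23 / 0.21, about 1 day. More than that, and the arm with more deaths shows more days.

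**Step 5: a second set of assumptions.** Over 182 days with mortality of 30% v 10% and r = 15%, the higher-mortality arm averages about 3.0 fewer days and is significantly favoured in 9.7% of trials. Adding 14 extra hospital days before each death shrinks the difference to 0.3 days and the percentage to 3.0%.

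**The case against.** The strongest reply is that the article condenses a fuller protocol, that an analysis plan may exist, and that scoring of deaths in a secondary resource-use outcome is often settled there. Section 2.16 gives a generic list of tests and assigns none to these totals by name. This is fair, and bare silence would not be a finding. But the article does fix the outcome as a raw total, applies its analysis section to all measurements, and gives a general imputation rule. Those stated choices do not suit an outcome truncated by death.

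A reader might go further and infer that the arm with earlier deaths will look better on all three outcomes. The documents do not support that. They give no mortality rate and no reason to expect a difference between arms; without a difference in mortality or its timing there is no systematic bias. Dying patients may also use more inpatient care, and steps 4 and 5 show that this can offset the truncation. For ICU and ventilation about one extra day per death suffices at a 1% rate, so no direction can be claimed there. The 4 to 7 days concern hospital stay only and amount to no more than about one standard error in a trial of this size.

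It is also true that these are secondary outcomes and that mortality is reported at 3 and 6 months, so a large imbalance would be visible. That helps a reader suspect a problem but does not correct the comparison or its P value.

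**Conclusion.** The point stands in a limited form. As defined, the three totals take no account of death, although the protocol expects many deaths. If mortality or its timing differs between arms, the totals can mislead: truncation by early death can make the worse arm look better, and inpatient days before death can cancel or reverse that. A total that can move either way as deaths increase cannot be read as benefit or harm.

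The size of 4 to 7 hospital days rests on assumed 6-month mortality of 20% to 40% in the better arm, a doubled hazard in the other, equal hospital use on 25% of days alive, and no extra days before death. The main outcomes (weight, BMI and the dumping scores) are outside this point. The change is worth making before the data are analysed, but it does not threaten the trial's principal conclusions.

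**What to change.** Replace the three compared outcomes with days alive and out of hospital, days alive and out of ICU, and days alive and off the ventilator, each from randomisation to 6 months, with days after death counted as 0. Compare them by Mann–Whitney U. State that days after death are not missing and will not be imputed. Show the raw totals descriptively beside the number of deaths in each arm.

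The cost is mainly a change of definition, since stay, ventilation and mortality are already collected; the exact date of death is needed, not only status at 3 and 6 months. The drawback is that the composite mixes death with length of stay. For ICU and ventilation, where few days are used, it will mostly reflect survival, so mortality must still be reported separately. A worst rank for death is an alternative, provided one rule is fixed in advance.
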